### 2.4. Sample Size Calculation

Sample size was estimated a priori using G*Power 3.1 [37]. Maximal voluntary contraction pressure (mmHg), assessed by manometric perineometry, was selected as the single primary outcome because it provides an objective and quantitative measure of PFM strength and is the outcome most directly related to the primary study hypothesis.

Previous randomized controlled trials involving women with UI have shown that vaginal manometric measures of PFM strength and endurance are responsive to exercise-based interventions incorporating specific or voluntary PFM contractions. In particular, Gonzaga et al. [38] reported improvements in manometric measures of PFM strength and endurance following PFM training and Pilates exercise performed with voluntary PFM contraction in postmenopausal women with UI. However, because previous studies are characterized by relatively small sample sizes and heterogeneous interventions and do not provide either a directly applicable standardized effect size or an established clinically important difference for the planned group-by-time comparison, Cohen’s f = 0.24 was selected as a conservative a priori planning assumption rather than an empirically derived effect estimate [39,40].

The calculation was based on a repeated-measures ANOVA model (within-between interaction; four groups; three time points: T0, T1, T2; two-tailed α = 0.05; statistical power = 1 − β = 0.80; assumed correlation among repeated measures r = 0.50; and Cohen’s f = 0.24). Under these assumptions, the minimum analytical sample required was estimated at 96 participants. Nevertheless, the planned recruitment target was set at 120 participants (30 per group). This target exceeds the minimum sample size required by the formal power calculation and was selected to preserve balanced allocation across the four intervention groups, accommodate anticipated attrition and incomplete follow-up data, and improve the precision and stability of the estimated longitudinal treatment effects obtained from the planned linear mixed-effects models (LMM). The anticipated attrition rate was conservatively estimated at 20%, based on participant retention reported in comparable randomized exercise-based interventions involving older women with UI [7,41,42].

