### 2.5. Randomization and Blinding

Randomization will be performed after completion of baseline assessment and informed consent procedures. An independent researcher not involved in participant recruitment, intervention delivery, outcome assessment, or data analysis will generate the allocation sequence using the Sealed Envelope^TM^ (London, UK) online randomization tool, with a 1:1:1:1 allocation ratio.

Allocation concealment will be ensured using sealed, opaque, consecutively numbered envelopes prepared according to the generated sequence. The envelopes will be kept by an independent researcher and opened sequentially only after each participant has completed baseline assessments and provided written informed consent. Outcome assessors and data analysts will remain blinded to group allocation throughout the study.

Due to the nature of the intervention, participants and intervention providers cannot be blinded. Several measures will be implemented to minimize performance and detection bias. First, participants will be informed that they will be randomly assigned to one of several intervention approaches. However, they will not be provided with information regarding the specific study hypotheses or the intervention received by the other groups. Participants will be told that the study evaluates different approaches to improving physical function and urinary control in older women, without reference to the specific components assigned to each group. Second, exercise sessions for different intervention groups will be scheduled at separate time slots throughout the week, ensuring that participants from different groups do not share waiting areas, changing rooms, or common spaces during study activities. This separation of session schedules minimizes the risk of contamination and inadvertent unblinding. Third, participants randomized to the control group will receive their educational sessions in a separate setting and at different times from the exercise groups.

Given the multidimensional nature of the intervention, blinding of the intervention supervisor and the physiotherapist delivering the sessions is not possible. However, a standardized supervision checklist will be used to ensure intervention fidelity across sessions and minimize intervention-delivery drift.

A flow diagram describing the anticipated participant progression throughout screening, randomization, allocation, follow-up, and analysis phases is presented in Figure 1.

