### 2.8. Statistical Analysis

#### 2.8.1. Data Analysis Plan

All statistical analyses will be performed using IBM SPSS Statistics (version 29) and R (version 4.3, R Core Team, 2024). All tests will be two-tailed, with statistical significance set at *p* ≤ 0.05. Descriptive statistics (means, standard deviations, frequencies, and percentages, as appropriate) will be reported for all sociodemographic, clinical, and outcome variables at each assessment time point.

Analyses will follow the intention-to-treat (ITT) principle, including all randomized participants in the groups to which they were originally allocated, regardless of intervention adherence or study completion. As a sensitivity analysis, a per-protocol analysis will also be conducted including only participants who attended ≥ 80% of scheduled sessions and completed all assessment time points.

The primary analysis will be conducted using likelihood-based estimation within the cLDA framework, which incorporates all available observations under the missing-at-random (MAR) assumption. Missing data patterns, including Little’s MCAR test, will be explored descriptively but will not determine the primary analytical approach. Multiple imputation by chained equations (MICE) will be performed as a pre-specified sensitivity analysis to evaluate the robustness of the primary findings.

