To address H4, pre-specified exploratory association analyses will be conducted within the intervention groups combined (EX, EXVERB, and EXVERBPSY; *n* ≈ 90). To reduce potential regression-to-the-mean bias, baseline-adjusted residualised change scores will be used instead of raw change scores. Residualised change scores will be obtained as the residuals from linear regression models in which each post-intervention (T1) or follow-up (T2) value is regressed on its corresponding baseline (T0) value. Separate residualised change scores will therefore be adjusted for the T1 (post-intervention) and T2 (follow-up) assessments, each adjusted for its corresponding baseline (T0) value. For the Short FES-I, lower scores indicate improvement; therefore, more negative residualised values will reflect greater reductions in fear of falling.

Three sequential analyses will be performed: (1) Pearson or Spearman correlations between residualised psychological change scores and intervention adherence (percentage of sessions attended); (2) correlations between residualised psychological change scores and residualised change scores in the primary endpoint (Δmaximal voluntary contraction pressure assessed by manometric perineometry) and prespecified secondary outcomes at T1 and T2; and (3) hierarchical multiple regression analyses conducted within the intervention groups, in which group allocation (EX, EXVERB, EXVERBPSY) is entered in Step 1 and residualised psychological change scores are added in Step 2, with residualised change in the primary endpoint and, separately, each secondary outcome entered as the dependent variable. The increment in R^2^ (ΔR^2^) will be reported as the indicator of additional variance explained beyond group assignment.

All H4 analyses are designated as exploratory and hypothesis-generating. No adjustment for multiple comparisons will be applied, and findings will be interpreted cautiously with emphasis on effect estimates, 95% confidence intervals, and the consistency of observed associations rather than on statistical significance alone. These analyses do not constitute a formal mediation analysis and do not permit causal inference about psychological mechanisms.

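### The H4 adherence correlation pools three randomised arms without a term for arm, and no other H4 analysis supplies an arm-adjusted version

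*Protocol article*

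**What the plan says.** All from the protocol article, section 2.8.1 unless stated.

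- The H4 analyses are "conducted within the intervention groups combined (EX, EXVERB, and EXVERBPSY; *n* ≈ 90").
- Each change score is the residual from regressing the T1 or T2 value on its own baseline. Arm is not in that regression.
- Analysis (1) is "Pearson or Spearman correlations between residualised psychological change scores and intervention adherence (percentage of sessions attended").
- Analysis (2) is "correlations between residualised psychological change scores and residualised change scores in the primary endpoint" and in the secondary outcomes.
- Analysis (3) is a hierarchical regression with arm in Step 1 and psychological change in Step 2. Its dependent variables are the residualised change in the primary endpoint and, separately, in each secondary outcome. Adherence is not among them.
- All H4 analyses are labelled exploratory, without multiplicity adjustment. The section says that they are not a mediation analysis and support no causal claim about psychological mechanisms.

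H4 itself (Introduction) has two halves: that psychological improvement goes with higher adherence, and that it goes with better outcomes. Under section 2.6 only EXVERBPSY receives the psychoeducational sessions. The Introduction and section 2.6.10 expect those sessions to improve emotion regulation and self-efficacy and to sustain adherence.

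**The concern.** Residualising on baseline removes baseline differences between women but leaves differences between arm means at T1 and T2. If one arm has higher means on both variables, pooling the arms adds a between-arm component to the correlation. That component has the sign H4 predicts (taking scores so that higher means better; the Short FES-I runs the other way). It appears even if, within every arm, women who improve more psychologically attend no more sessions.

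The trial's own premises predict this pattern for psychological change and adherence. For the clinical outcomes a reader can turn to analysis (3) for an estimate net of arm. For adherence there is nothing to turn to. A positive pooled coefficient could then be reported as support for the adherence half of H4 when part or all of it restates the randomised comparison of EXVERBPSY with the other two arms.

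**Working it through.** **Inputs from the document**
- Recruitment: "planned recruitment target was set at 120 participants (30 per group"), "with a 1:1:1:1 allocation ratio" (sections 2.4 and 2.5).
- Attrition: "The anticipated attrition rate was conservatively estimated at 20"% (section 2.4).
- Level: "All tests will be two-tailed, with statistical significance set at *p* ≤ 0.05" (section 2.8.1).

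**Input assumed.** EXVERBPSY differs from EX and EXVERB by d₁ within-arm SD on psychological change and d₂ on adherence. There is no within-arm correlation. The document gives no values, so d = 0.5 and 0.8 are shown as a range.

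**Step 1. The stated n.** 3 arms × 30 = 90, so the plan's figure is reproduced as the randomised count. Applying 20% attrition equally to each arm: 90 × 0.80 = 72, or 24 per arm, with observed change scores.

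**Step 2. Induced correlation for adherence.** With one arm of three shifted on both variables:
- between-arm covariance = d₁ × d₂ × (1/3) × (2/3) = (2/9) d₁d₂
- total variance of each variable = 1 + (2/9) d²
- r = (2/9) d₁d₂ / √[(1 + (2/9) d₁²)(1 + (2/9) d₂²)]

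For d₁ = d₂ = 0.5: 0.0556 / 1.0556 = 0.053.
For d₁ = d₂ = 0.8: 0.1422 / 1.1422 = 0.125.

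**Step 3. Chance of p < 0.05 with no within-arm association.** By Fisher's z, with λ = atanh(r) × √(n − 3), the probability is 1 − Φ(1.96 − λ) + Φ(−1.96 − λ).

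| d on both | r | n = 72 | n = 90 |
|---|---|---|---|
| 0.5 | 0.053 | 7.2% | 7.8% |
| 0.8 | 0.125 | 18.0% | 21.5% |

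Worked case, d = 0.8 and n = 72: λ = 0.125 × √69 ≈ 1.04. The upper tail beyond 1.96 − 1.04 = 0.92 is about 17.9%, and the lower tail adds about 0.1%.

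**Step 4. Comparison: psychological change against pelvic floor strength.** If the psychological shift is in EXVERBPSY only and the strength shift is equal in both verbal-cue arms, the covariance is d₁d₂/9 with the same variances. This gives r = 0.0278/1.0556 = 0.026 at 0.5/0.5 and 0.0711/1.1422 = 0.062 at 0.8/0.8. At n = 72 the chance of p < 0.05 is 5.5% and 8.1%.

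**Step 5. Does adjusting for arm cure it?** A simulation of the Step 4 pattern (4000 runs per setting, baseline-residualised scores) at shifts of 0, 0.5 and 0.8 compared the crude correlation with the Step 2 test of analysis (3). At 0.8 the crude correlation was significant in 11.2% of runs at n = 90 and 9.4% at n = 72. The arm-adjusted test stayed between 4.5% and 5.0% in every setting. Its crude rates differ slightly from the formula because its shifts are in SDs of the raw score rather than of the residual.

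**Step 6. What 72 instead of 90 does to precision.** The critical |r| at two-sided 0.05 moves from 0.207 to 0.232. The r detectable with 80% power moves from 0.292 to 0.325.

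**The case against.** The strongest reply has four parts.

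1. *Causal readings are already ruled out.* A reader might infer that the plan would present arm differences as a psychological mechanism. The document does not support that: section 2.8.1 calls H4 exploratory, disclaims mediation and causal inference, and puts estimates and intervals ahead of significance. This stands and limits the consequence. It does not correct the adherence estimate, which remains the only one offered.

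2. *Arm adjustment is already planned.* A reader might infer that the whole of H4 lacks it. That is also unsupported. Analysis (3) reports the variance explained beyond arm for the primary endpoint and every secondary outcome, and showing crude correlations before an adjusted model is ordinary practice. This stands for the outcomes, so analysis (2) need not be replaced. It does not reach adherence.

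3. *The pooled correlation matches H4's wording*, which speaks of participants in the intervention groups and not of women within each arm. That is fair as a literal reading. But a pooled coefficient cannot distinguish an association between women from a difference between arms, and the plan itself expects the latter.

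4. *The stated n is not wrong.* A reader might take n ≈ 90 as a sample-size error. It is the randomised count, marked approximate, and no H4 power claim rests on it. The figure of 72 carries assumptions of its own: equal attrition across arms, the full 20% lost at the time point analysed, and no imputed data used for H4.

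The bias is also small unless EXVERBPSY has a sizeable advantage on both variables, and no such effect is given in the document.

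**Conclusion.** The point holds for the adherence analysis. Analysis (1) is a pooled correlation with no term for arm, and nothing else in the H4 plan supplies an arm-adjusted estimate, although the plan expects one arm to be higher on both variables. The induced correlation is about 0.05 to 0.12 and the false-positive rate about 7% to 18% at n = 72. These figures assume a shift of 0.5 to 0.8 SD in EXVERBPSY on both variables, no within-arm association, equal arms and Pearson correlation. At the lower end the distortion is slight, and it grows the better the psychoeducation works.

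For the clinical outcomes the arm-adjusted evidence is already planned, and only its precedence over the crude correlations needs stating. No confirmatory conclusion of the trial is affected. This is a minor improvement without cost.

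**What to change.** - Report the association between psychological change and adherence adjusted for arm. Any of three routes will do: a partial correlation given arm, correlation of arm-centred scores, or adherence as a further dependent variable in the analysis (3) regression.
- State that for the primary endpoint and secondary outcomes the arm-adjusted results of analysis (3) are the H4 evidence, and that the correlations of analysis (2) are descriptive.
- Optionally, say that about 90 is the number randomised and that about 72 would have observed change scores if the 20% attrition falls equally on the three arms.

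Cost: a few words in section 2.8.1. Arm is already recorded and already used in analysis (3), so no data collection, sample size or other analysis changes. The adjustment spends two degrees of freedom.

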**H4.** 
*Among participants in the intervention groups, greater residualised improvements in psychological well-being (SF-36 Mental Component Summary score) and fear-of-falling-related self-efficacy (FES-I Short) from T0 to T1 will be positively associated with higher intervention adherence and with greater residualised improvements in the primary endpoint (maximal voluntary contraction pressure assessed by manometric perineometry) and the prespecified secondary outcomes at T1 and T2.*

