Additionally, static posturography will be used to analyze center-of-pressure (COP) displacement under different sensory conditions using the NedSVE/IBV^®^ system on a Dinascan/IBV force platform. The following COP variables will be collected: sway area (mm^2^) and maximum anteroposterior (AP) and mediolateral (ML) displacement (mm). Static posturography have demonstrated good clinical utility and moderate-to-high test–retest reliability in bipedal standing tasks under different sensory conditions [74,75].

I.Fear of falling

Fear of falling will be assessed using the short Falls Efficacy Scale–International (FES-I). In the present study, a shortened and validated Spanish version will be used, which assesses confidence in performing daily 7 activities associated with balance demands and fall risk. Higher total scores indicate greater concern about falling. This version has demonstrated adequate psychometric properties in Spanish-speaking populations [76]. Total scores will be used for statistical analysis.

J.Quality of life

Health-related quality of life will be assessed using the 36-Item Short Form Health Survey (SF-36), which evaluates eight domains of physical and mental health. Domain scores range from 0 to 100, with higher scores indicating better perceived health status and quality of life [77].

K.Psychological and social well-being

Self-esteem will be assessed using the Rosenberg Self-Esteem Scale (RSES), a widely used measure of global self-esteem. The scale consists of 10 items rated on a 4-point Likert scale, with total scores ranging from 10 to 40, and higher scores indicating higher self-esteem [78].

L.Physical Activity Questionnaire-Short Form (IPAQ-SF)

Physical activity levels will be assessed using the IPAQ-SF, a validated self-report questionnaire which records physical activity performed during the previous 7 days. Data will be processed according to the official IPAQ scoring protocol and expressed as total physical activity (MET-min/week). Participants will also be classified into the standard IPAQ physical activity categories (low, moderate, or high). Data cleaning and truncation procedures will follow the official IPAQ data processing guidelines. The IPAQ-SF will be administered at baseline (T0) and at the 6-month follow-up assessment (T2).

M.Body weight and composition

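### H4 tests its psychological predictors against every secondary outcome without excluding Short FES-I and SF-36, the instruments that supply them, so some associations arise by construction

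*Protocol article*

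**What the plan says.** H4, in the Introduction, fixes the predictors and their window: "greater residualised improvements in psychological well-being (SF-36 Mental Component Summary score) and fear-of-falling-related self-efficacy (FES-I Short) from T0 to T1". It expects these to go with higher adherence and with greater residualised improvement in the primary endpoint and in "the prespecified secondary outcomes at T1 and T2".

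Section 2.7.2 lists both source instruments as secondary outcomes. Short FES-I stands under item I and is analysed as a total score. SF-36 stands under item J as an instrument "which evaluates eight domains of physical and mental health". The scoring given there is "Domain scores range from 0 to 100", and the MCS is not named. Item K, whose heading refers to psychological well-being, holds the Rosenberg scale.

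Section 2.8.1 addresses H4 in the three exercise arms combined (n ≈ 90). A residualised score is the residual from regressing the T1 or T2 value on the T0 value: "Separate residualised change scores will therefore be adjusted for the T1 (post-intervention) and T2 (follow-up) assessments". Three analyses follow:

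1. Correlation of the psychological change scores with attendance.
2. Correlation with residualised change in the primary endpoint and the secondary outcomes at T1 and T2.
3. Hierarchical regression, with group in Step 1 and the psychological scores in Step 2, and with "residualised change in the primary endpoint and, separately, each secondary outcome entered as the dependent variable".

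No outcome is excluded. All H4 analyses are labelled exploratory, without multiplicity adjustment and without causal claim.

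**The concern.** If every secondary outcome serves as a dependent variable, the set includes Short FES-I and the SF-36 scores. Short FES-I change then appears on both sides of the equation, and SF-36 domains are related to a summary composed of domains. Such associations say nothing about whether psychological change goes with change in pelvic floor, continence or physical outcomes, which is what H4 is about.

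The exploratory label does not remove the problem. Section 2.8.1 asks readers to weigh effect sizes, intervals and how consistently the associations point one way. For Short FES-I and the mental domains of SF-36, the built-in associations run in the direction that H4 predicts, so they would add to its apparent support.

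**Working it through.** **Inputs.**
- Analysis set: 3 arms × 30 = 90, which reproduces the plan's n ≈ 90. With the 20% attrition of Section 2.4, 90 × 0.8 = 72.
- Correlation among repeated measures: r = 0.50 (Section 2.4). The plan states it for the primary endpoint; using it for Short FES-I and SF-36 is an assumption.
- SF-36 weights: not in the document. Assumed: the summary is an equal-weight sum of k domains, with k from 4 to 8.

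**Short FES-I at T1.** Predictor and outcome are the same residual (T1 regressed on T0), so r = 1 and the Step 2 R² is 1. No assumption is needed.

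**Short FES-I at T2 on its T0-to-T1 change.** Both are residuals on the same baseline, so their correlation is the partial correlation of T1 and T2 given T0. With a common correlation r this is

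(r − r²)/(1 − r²) = r/(1 + r).

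At r = 0.50: (0.50 − 0.25)/(1 − 0.25) = 0.33. As a range, r = 0.3 gives 0.3/1.3 = 0.23, and r = 0.7 gives 0.7/1.7 = 0.41.

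**SF-36 domain at T1 against a summary that contains it.** For k independent domain changes of equal variance, the part-whole correlation is 1/√k.
- k = 8: 1/√8 = 0.35, R² = 0.125.
- k = 4: 1/√4 = 0.50, R² = 0.25.

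By the Fisher z approximation, the chance of p < 0.05 from this overlap alone is 87% (n = 72) to 93% (n = 90) for r = 0.35, and over 99% for r = 0.50.

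**SF-36 domain at T2 against the T0-to-T1 summary.** The part-whole value is multiplied by the 0.33 above: 0.35 × 0.33 = 0.12 (k = 8) and 0.50 × 0.33 = 0.17 (k = 4).

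**Simulation of analysis 3.** There were 1,000 trials, with no arm effect and no link between the psychological scores and any other outcome. The visit correlation was 0.50. The MCS was the mean of four mental domains, with inter-domain correlation 0 or 0.4. Both T0-to-T1 predictors entered in Step 2.

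| Dependent variable | Mean r with its own-instrument predictor | ΔR² at Step 2 | Significant, n = 90 | Significant, n = 72 |
|---|---|---|---|---|
| Short FES-I, T1 | 1.00 | 0.97–0.98 | 100% | 100% |
| Short FES-I, T2 | 0.33 | 0.12–0.13 | 81% | 74% |
| SF-36 mental domain, T1 | 0.50–0.74 | 0.26–0.54 | 99–100% | 98–100% |
| SF-36 mental domain, T2 | 0.16–0.25 | 0.05–0.09 | 27–53% | 22–46% |
| Primary endpoint, T1 (no overlap) | none (r with either score about 0) | 0.02–0.03 | about 5% | about 5% |

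In the first row, ΔR² falls just short of 1 only because group takes 0.02 to 0.03 by chance in Step 1. The upper SF-36 values also reflect the assumed correlation between domains, so they are not pure part-whole overlap. The last row shows the procedure rejecting at its nominal rate once the outcome no longer supplies a predictor.

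**The case against.** The strongest reply is that H4 is exploratory, is to be read with caution and not on significance alone, and touches no confirmatory result. Short FES-I regressed on itself would be seen at once as an identity. Only two of the many instruments in Section 2.7.2 are affected. This limits the weight of the point. It does not answer the T2 association of Short FES-I or the SF-36 part-whole associations, which are not obvious in a table of results. Nor does it alter the fact that the analysis rule as written includes them.

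The SF-36 figures are fairly open to challenge. They rest on assumed equal weights. The larger ones hold only at T1, and their size and direction are not established for domains outside the mental ones.

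A reader might go further and infer that hypothesis, outcome list and analysis contradict one another on the predictor's time window and SF-36 score. The documents do not support that. The outcome list gives visits and no change window. Section 2.8.1 names no SF-36 score, so it cannot name a different one. Its T1 and T2 residualised scores are needed for H4's outcomes at those visits, and H4 itself limits the predictor to T0–T1. The Rosenberg scale's place under item K creates no conflict, because H4 names its instrument. What remains is that Section 2.8.1 does not repeat the predictor's window or score, and that item J describes only domain scores. This is an ambiguity, and H4 resolves it.

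**Conclusion.** The point holds for own-instrument overlap. Without an exclusion, the H4 analyses include one identity (Short FES-I at T1, r = 1, free of assumptions) and one persistence correlation within a single instrument (Short FES-I at T2, about 0.33 if r = 0.50 applies, 0.23 to 0.41 for r from 0.3 to 0.7). They also include SF-36 part-whole associations: about 0.35 to 0.50 at T1 under equal weights and independent domains, and about 0.12 to 0.17 at T2 under the same assumptions.

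It would be too strong to conclude that every Short FES-I or SF-36 outcome is compromised. Short FES-I change against an SF-36 domain, or MCS change against Short FES-I, is not circular. The primary analysis and the planned group contrasts are untouched. This is a minor correction, worth making because it is cheap.

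**What to change.** In the H4 paragraphs of Section 2.8.1:

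- State the predictors as T0-to-T1 residualised change in the SF-36 MCS and Short FES-I, for outcomes at both T1 and T2, as H4 does.
- In analysis 2, do not correlate Short FES-I change with Short FES-I outcomes, or MCS change with the MCS or SF-36 domain outcomes. Cross-instrument correlations may stay.
- In analysis 3, where both predictors enter Step 2 together, exclude Short FES-I, the MCS and the SF-36 domains as dependent variables. Alternatively, use only the non-overlapping predictor for each of them.

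In Section 2.7.2 J, name the MCS as the SF-36 score used for H4.

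The cost is a few sentences of wording and the loss of a few exploratory associations that could not have informed H4. Sample size, data collection and the primary analysis do not change.
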